## Abstract

**Background:** Pregnancy anemia remains as a public health problem, since the official reports in the 70's. To guide the treatment of iron-deficiency anemia in pregnancy, the haemoglobin concentration is the most used test in spite of its low accuracy, and serum ferritin is the most reliable test, although its cutoff point remains an issue.

**Methods/design:** The aim of this protocol is to verify the accuracy of erythrocyte indices and serum ferritin (studied tests) for the diagnosis of functional iron-deficiency in pregnancy using the iron-therapy responsiveness as the gold-standard. This is an ongoing phase III accuracy study initiated in August 2011 and to be concluded in April 2013. The subjects are anemic pregnant women (haemoglobin concentration < 11.0 g/dL) attended at a low-risk prenatal care center in the Northeast of Brazil. The sample size ( $n$  278) was calculated to estimate sensitivity of 90% and 80% of specificity with relative error of 10% and power of 95%. This study has a prospective design with a before-after intervention of 80 mg of daily oral iron during 90 days and will be analyzed as a delayed-type cross-sectional study. Women at the second trimester of pregnancy are being evaluated with clinical and laboratorial examinations at the enrollment and monthly. The 'responsiveness to therapeutic test with oral iron' (gold-standard) was defined to an increase of at least 0.55 Z-score in haemoglobin after 4 weeks of treatment and a total dose of 1200 mg of iron. At the study conclusion, sensitivities, specificities, predictive values, likelihood ratios and areas under the ROC (Receiver Operating Characteristic) curves of serum ferritin and erythrocyte indices (red blood cell count, haematocrit, haemoglobin concentration, mean corpuscular volume, mean corpuscular haemoglobin, mean corpuscular haemoglobin concentration, red blood cell distribution width, reticulocyte count) will be tested. The compliance and adverse effects are considered confounding variables, since they are the main obstacles for the iron-therapy responsiveness.

**Discussion:** This study protocol shows a new approach on iron-deficiency anemia in pregnancy from a functional point of view that could bring some insights about the diagnostic misclassifications arising from the dynamic physiologic changes during the gestational cycle.

**Trial registration:** WHO International Clinical Trials Registry Platform U1111-1123-2605.

## Background

Iron-deficiency anemia is recognized as the nutritional deficiency of highest prevalence in the world, reaching all continents and geo-economic blocks [1,2]. This is a serious problem in the gestation-puerperal period since the maternal anemia is associated with several adverse perinatal outcomes, such as prematurity, low birth weight and rates of maternal and perinatal mortality [3-9]. For instance, the relationship between maternal anemia and perinatal mortality contributed with 56% of 800,000 deaths attributed to iron-deficiency anemia globally in 2000 [9]. Hence, universal supplementation of iron during pregnancy has been widely recommended as a health policy from the 70's [1,10]. However, the prevalence of gestational anemia remains 50% globally and 20% in the Americas since then [1,2] which points to the failure of this measure, despite the effectiveness of the iron supplementation programs in the general population has been estimated to about 70% [1].

Apart of the concerning issues to the implementation degree and quality of the programs to control anemia, the main limiting factor of the effectiveness and efficacy of the interventions with iron supplements would be the poor compliance to therapy, which can achieve figures up to 70% at pregnancy [11,12] and is associated with the frequent occurrence (20-70%) of gastrointestinal adverse effects [13-18]. Taking into account that the therapeutic success depends on the total dose of iron ingested throughout the treatment [14,18], higher cure rates of anemia should be observed in the controlled context of clinical trials, whereas the therapeutic compliance would be maximized, however, these rates are around 50% [19,20]. Therefore, factors not related to the therapeutic dose of iron may be contributing to these modest results, among them could be mentioned the criteria used to indicate and evaluate the iron-therapy during pregnancy [1,2,10].

The haemoglobin concentration (Hb) has been considered as a *proxy* of iron deficiency and widely recommended as a criterion for the indication of iron-therapy in pregnant women, particularly in location with few resources [1]. The Hb cutoff point of 11.0 g/dL for pregnancy was defined from North American and European reference populations by the Gaussian paradigm: less than 2 standard deviations below the mean reference [1,21,22]. This is a theoretical statistic definition that assumes prevalence of 5% for all disorders and might not be suitable for all epidemiologic or clinical settings [23]. Indeed, the 70's guideline of the World Health Organization (WHO) considered that the Hb cutoff points defined from population distributions could be an oversimplification [10]; and some studies have observing that Hb and other erythrocyte indices present low correlation with the body iron reserves in pregnant women (sensitivity and specificity

around 60%) [24-29]. Thus, could be considered that diagnostic misclassifications of iron-deficiency anemia may be another limiting factor of the iron-therapy responsiveness in this life cycle phase.

In fact, the cross-sectional and longitudinal assessment of the haematological profile during pregnancy is troublesome due to increased iron requirements beside the haemodilution, a physiological phenomenon in which occur an increase of 50% in the plasma volume *versus* 30% in the erythrocyte mass [1,21]. This phenomenon is responsible for the U-shaped curve that Hb and haematocrit levels develop in pregnant women with nadir between the 24th and 28th weeks of pregnancy [24,30-32], which explains the "physiological anemia" in which the erythrocyte mass remains normal in relation to the effective body weight [1,7]. Based on this rationale, Beaton and McCabe (1999) developed the Hb Z-score methodology to correct its values according to the mean expected for the gestational week [33]. An alternative to a more accurate diagnosis of iron deficiency would be the dosage of biomarkers of iron metabolism, however, these are also influenced by gestational physiology and many have not been standardized to be used at pregnancy [1,34]. The serum ferritin remains as the biomarker that best correlates with the iron content in the bone marrow of pregnant women [24-27], but there is no consensus as to its cut-off point [1,34].

These observations indicate that the accurate diagnosis of iron-deficiency anemia during pregnancy is problematic. The current diagnostic criteria with steady cutoff points based on Gaussian definition of normality does not reflect the functional conceptions of the anemia and of the iron deficiency at pregnancy, respectively, as the status of insufficient circulating haemoglobin for oxygen transport required by gestational metabolism and as the inadequate iron supply to achieve this demand [1]. So, the hypothesis of AMA study is that the pre-treatment values of Hb and other erythrocyte indices have low power to predict the functional iron-deficiency in pregnancy and to discriminate iron-sufficient from iron-deficient pregnant women (potentially responsive to iron-therapy). It is expected that the serum ferritin presents higher accuracy parameters than erythrocyte indices.

## Rationale for AMA study - phase III diagnostic accuracy study

Starting from the assumptions that erythrocyte indices have low accuracy for the diagnosis of iron deficiency in pregnant women in accuracy phase II studies [24-29], the AMA study was initiated. As an accuracy phase III study, it is being conducted in a population under a higher risk of iron deficiency [23]. Thereby, this study will evaluate and compare the accuracy of Hb and other erythrocyte indices and of serum ferritin for the diagnosis

of functional iron deficiency in anemic pregnant women ( $Hb < 11.0$  g/dL), as pregnant women with  $Hb > 11.0$  g/dL from the same location have very low rates of iron-deficiency [35].

In the absence of a gold standard to define functionally iron deficiency in pregnancy, was established as the reference standard the haematological response to oral iron-therapy, which is considered a reliable and low-cost alternative for the confirmation of anemia due to iron deficiency [1]. In this protocol, this approach considers the rationale of therapeutic definition of normality (therapeutic diagnostic) that employs the response to specific treatments in disease-target markers as the parameter to define diagnostic criteria [23]. This functional rationale is suitable for the pregnancy period because the dynamic physiologic changes on the erythrocyte indices and biomarkers of iron metabolism [30-34].

Taking into account that adverse effects and poor therapeutic compliance are the main limiting of intake of an effective dose of iron they were pre-established as confounding variables. Whereas the physiological fluctuation of Hb at each gestational week is a factor which can be bias the evaluation of the haematological response to iron-therapy [33], the pre and post treatment Hb values will be transformed into Z-scores for purposes to measure the outcome.

## Methods/design

### Study aim and objectives

The aim of this study is to describe and to compare, at the practice setting of prenatal care, the pragmatic utility of serum ferritin and each single test on erythrogram to discriminate iron-sufficient from iron-deficient pregnant women who will benefit from iron therapy to achieve the improvement of their anemia.

The *primary objective* of this study is to analyze the accuracy (sensitivity, specificity, predictive values, likelihood ratios and Receiver Operating Characteristic curves) of Hb and other erythrocyte indices and of serum ferritin (studied tests) to predict the 'responsiveness to therapeutic test with oral iron' (gold-standard test) in pregnant women pre-classified as anemic ( $Hb < 11.0$  g/dL).

As a *secondary objectives* are proposed to compare the results of evaluation of the 'responsiveness to therapeutic test with oral iron' using absolute values and Z-scores of Hb; and to describe the frequency of the therapeutic compliance and gastrointestinal adverse effects, as well as their association with the dose of iron intake and with the therapeutic response.

### Study design

This study deals with a diagnostic validation of the pre-treatment values of erythrocyte indices and serum ferritin

(studied tests) in relation to the gold standard 'responsiveness to therapeutic test with oral iron' in women with low-risk singleton pregnancy. The design is classified as phase III as these tests already have been used in clinical practice and will be evaluated in anemic pregnant women [23], i.e., a population under risk of iron deficiency (target disease) with formal indication of oral iron therapy in accordance with the criterion adopted by WHO ( $Hb < 11.0$  g/dL) [1]. The direction of the study is prospective (delayed-type cross-sectional study) with the purpose of observing the variation in the Hb values after a period of at least 4 weeks of a 'before-after' intervention with 80 mg of daily oral iron and to define the final diagnosis of the functional iron deficiency [36]. The measurement of target disease (iron deficiency) by the gold-standard ('responsiveness to therapeutic test with oral iron') has been carried out on all participants, such as post-treatment Hb has been assessed independently of the results of the studied tests (pre-treatment erythrocyte indices and serum ferritin). The final diagnosis of the functional iron deficiency will be blinded in relation to the tests results carried out at time-zero since it will be calculated by the Hb Z-scores methodology at the conclusion of the study.

The protocol is registered as a single-arm clinical trial in the Brazilian Clinical Trials Registry (REBEC) at the Ministry of Health of Brazil and in the WHO International Clinical Trials Registry Platform (U1111-1123-2605).

### Study setting and period

This study is set in the prenatal care center of *Instituto de Medicina Integral [name]* (IMIP) at a large urban center in the Northeast of Brazil. IMIP is a regional tertiary hospital with reference in maternal-child health which serves primarily for high-risk pregnant women; however, around 600 low-risk pregnant women are attended monthly. Data collection was initiated in August 2011 in a pilot study phase in which was concluded in October 2011. The conclusion of this study is scheduled for April 2013.

### Participants/eligibility criteria

The participants are 18-35 years old women with a low-risk singleton pregnancy. The inclusion criteria are Hb values  $\geq 7.0$  and  $< 11.0$  g/dL and the gestational age between 12 and 32 weeks. Pregnant women are being excluded if they have a history of hypersensitivity or intolerance to ferrous sulfate, mental deficits or disorders that cannot correctly follow the prescription; tobacco, alcohol or other drugs use; prior diagnosis of another cause of anemia; or at the time of inclusion present active infectious disease (positive serology for Human Immunodeficiency Virus or syphilis, leukocytosis or leukocyturia with positive urine culture).

# Recruitment, procedures and instruments

The recruitment procedure is a consecutive series of patients whose prenatal routine exams show anemia ( $Hb < 11.0$  g/dL) and encounters all other eligibility criteria (Figure 1). The pregnant women are then invited to participate in the study at the time of the prenatal consultation to then clarify about the issue. After reading and signing the written informed consent form, an initial consultation begins ( $C_0$ ) with a structured questionnaire and the anthropometric variables measurement (weight and height). At this moment, the prescription for the drug intervention proceeds under the proper guidance and then the pregnant woman is guided to perform the initial laboratory tests (complete blood count, reticulocyte count and serum ferritin).

The pregnant women are measured and weighed barefooted, without any objects in their hands or in their pockets on a calibrated electronic scale. It is requested that all pregnant women attend the laboratory in the morning within 8–12 hours of fasting to collect blood samples. The blood samples are collected and properly identified by the process of collecting in the routine service, through venipuncture in the antecubital fold. The erythrograms are analyzed using flow cytometry and absorbance of an automatic hematological analyzer (ABX Pentra DF120 Horiba brand) calibrated daily, and are complemented with a microscopic reading of smears stained with a panoptic dye to morphologically study of the cells. The reticulocyte count is performed by a manual method by reading of smears stained with brilliant cresyl blue dye. The serum ferritin is measured by chemiluminescence immunoassay in blood sample collected in dry tube,

using the same kit and following the calibration according to the international standards of WHO.

All non-laboratorial variables are obtained using a standardized form developed specifically for the research. The laboratory data are recovered directly by a computerized system of results generated electronically by the automated equipment of biological analysis. The laboratory tests of the pilot study ( $n$  23) were performed by the laboratory of the institution. After the conclusion of the pilot study (October 2011), for operational reasons, the laboratorial analysis service was outsourced to an external laboratory. Both laboratories have governmental certification and follow standardized operational norms.

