# Intervention

The treatment consists of two daily doses of 109 mg of ferrous sulfate in the form of pills with 40 mg of elemental iron (Hematofer®, Prati Donaduzzi & Cia LTDA). Three blisters with 20 pills are given at the enrollment ( $C_0$ ) and at the two monthly revaluations ( $C_1$ ,  $C_2$ ). The pregnant women are oriented at each consultation to ingest the medication with a glass of drinking water, 30 - minutes before a meal, and to preserve the non-consumed pills in the blisters. The safety profile for the use of ferrous sulfate at pregnancy is satisfactory; there were no reports of fetal damage or severe maternal adverse events [19,20]. The dose of 80 mg/daily of elemental iron was adopted due to the set of evidences not found any additional efficacy with higher daily doses [14,19].

[figure not shown]

**Figure 1** Flowchart of the participant enrolled in the AMA study until August 2012.

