### Operational and data analysis

The data are being released with dual input and processed in the EPIINFO3.4.2 program. The analytical design is as a delayed-type cross-sectional study, where at the end of the follow-up, the measured tests at time-zero (predictive variables) will be compared with the final diagnosis of the target-disease (outcome variable) to determine estimates of accuracy [36]. Thus, at the end, the proportions and its confidence intervals will be calculated for sensitivity, specificity, accuracy, predictive values, likelihood ratios and areas under the ROC curves of each erythrocyte index and serum ferritin against the presence or absence of the 'responsiveness to therapeutic test with oral iron'. The significance level adopted will be 5%. The estimates will be made according to the 3 × 3 table for the results distribution from diagnostic accuracy phase III studies, which have cells to report unconcluded

results (lost, not performed or indeterminate) of the gold standard and the studied tests [23]. This table enables to report the results unknown that could bias the measurement of accuracy at a clinical practice setting (Table 1).

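### The written sequence at enrolment (C0) does not ensure that blood labelled pre-treatment is drawn before the first iron pill

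*Protocol*

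**What the plan says.** Women are "invited to participate in the study at the time of the prenatal consultation". After consent, C0 begins with a questionnaire and measurements, and then "the prescription for the drug intervention proceeds under the proper guidance and then the pregnant woman is guided to perform the initial laboratory tests": the blood count, reticulocyte count and ferritin (Protocol, Recruitment, procedures and instruments). The same section adds: "It is requested that all pregnant women attend the laboratory in the morning", after 8 to 12 hours without food.

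The Intervention section states: "Three blisters with 20 pills are given at the enrollment". It continues: "The pregnant women are oriented at each consultation to ingest the medication with a glass of drinking water", 30 minutes before a meal.

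The results of that blood sample are labelled as untreated values throughout. Study design opens: "This study deals with a diagnostic validation of the pre-treatment values of erythrocyte indices and serum ferritin". The Rationale section and Gold-standard test speak of pre- and post-treatment haemoglobin, Studied tests calls the values initial, and Operational and data analysis places them at time zero.

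**The concern.** In a before-after diagnostic study, the timing of the index sample relative to the intervention is part of the design. Here one blood sample has two roles. It supplies every studied test, and its haemoglobin is the natural starting point for the Z-score change that decides who is a case. A draw made after iron has begun can therefore disturb both sides of the accuracy table: the test no longer describes untreated iron status, and any haemoglobin rise before the draw is missing from the measured response.

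The stated order is prescription first and laboratory second. Pills are issued at C0, and the draw requires a fast that a woman approached at a routine consultation may not have kept. No section holds the first pill until the draw, limits the interval from C0 to the draw, or asks for the two dates. The Discussion itself reports difficulty with patients' return visits and with getting laboratory tests done, so some delay is plausible.

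**Working it through.** **Text side by side.** The order under Recruitment is prescription, then laboratory referral. Intervention issues 3 × 20 = 60 pills at C0 with instructions for taking them. The sampling condition is a fasting morning attendance. Study design, Gold-standard test and Operational and data analysis assume that the result is pre-treatment. No sentence connects the procedure to the label.

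**The plan's own figures.** The minimum dose is 30 pills × 40 mg = 1200 mg, as stated. The response threshold is 0.55 × 0.9 g/dL = 0.495 g/dL, which the protocol rounds to 0.5. Both reproduce.

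**Illustration of scale.** The delay *d* from first pill to draw is not in the document, so it is assumed, with full intake of 80 mg a day.

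- Dose before baseline = 80 × *d*; share = 80*d*/1200.
- For haemoglobin, assume further a linear rise, a final sample fixed at day 28 and no shift in the reference mean. A true 28-day rise of 0.5 g/dL is then measured as 0.5 × (1 − *d*/28)/0.9 Z.
- The true 28-day rise needed to reach the threshold is 0.495/(1 − *d*/28).

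| *d* (days) | Iron before baseline (mg) | Share of 1200 mg | Measured change (Z) | True rise needed (g/dL) |
|---|---|---|---|---|
| 0 | 0 | 0% | 0.556 | 0.495 |
| 1 | 80 | 7% | 0.536 | 0.513 |
| 3 | 240 | 20% | 0.496 | 0.554 |
| 7 | 560 | 47% | 0.417 | 0.660 |

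Under these assumptions, women whose true rise lies between 0.495 and 0.554 g/dL (3 days) or between 0.495 and 0.660 g/dL (7 days) would change from case to non-case. If the deciding haemoglobin is instead taken at day 90, with a linear rise over that period, the upper limits fall to 0.495/(1 − 3/90) = 0.512 and 0.495/(1 − 7/90) = 0.537 g/dL.

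**Dose between the two readings.** The 30-pill minimum is not tied to the draw. A woman who takes exactly 30 pills, 14 of them before a day-7 draw, meets the minimum, but only (30 − 14) × 40 = 640 mg falls between her two haemoglobin values.

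**Ferritin and reticulocytes.** The document gives no time course for either after iron starts, so no size is put on that part.

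**The case against.** The strongest reply is that the protocol is only silent on one operational link. Prescribing is not ingesting, the order prescription then test is compatible with a pre-pill draw, and a site procedure may already secure it. A reader might infer that the draw takes place at a separate later visit, or that women hold the pills before they reach the laboratory. The text states neither: a woman already fasting at a morning consultation could be sampled the same day, and Intervention gives no order between dispensing and sampling within C0. A reader might also take 20% and 47% as shares of the lost haemoglobin effect. They are shares of dose under assumed delays; the protocol ties most of the effect to 1200 mg but gives no time course. The 0.5 g/dL example sits only 0.006 Z above the threshold, so almost any shift reclassifies it, and later monthly readings shrink the effect. Finally, a qualifying haemoglobin from routine tests precedes C0.

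All of this limits the size and certainty of the problem. It does not remove it. The written order permits the error, and no sentence prevents it. The qualifying haemoglobin is not named as the baseline, and ferritin and reticulocytes are listed only among the tests that follow the prescription.

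**Conclusion.** The point holds as a gap between procedure and label: the sequence as written permits on-iron index tests and baseline haemoglobin in a study that treats them as pre-treatment. It does not show that this happened in any woman. The effect is nil if every draw was made before the first pill, and it grows with the delay; for haemoglobin it is confined to women near the threshold. The illustrated sizes rest on the assumed delays, full intake from C0 and, for haemoglobin, a linear rise. The conclusion rests on the protocol's text, without the Figure 1 flowchart. It deserves correction because the affected sample underlies every accuracy estimate and the remedy is cheap.

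**What to change.** Reconcile Recruitment, procedures and instruments and Intervention with the pre-treatment label by placing the C0 blood draw before any study iron is taken. From now on, record the draw date and the first-pill date for each woman.

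For women already enrolled, compare the laboratory draw date with the C0 date. Results come from a computerised laboratory system, so draw dates may be recoverable, and the planned interim look at 186 women is a convenient occasion. This interval is a proxy, because the first-pill date may be unknown. Report its distribution. Keep all women in the main analysis, and add a sensitivity analysis restricted to same-day draws or draws known to precede the first pill. Moving women to the indeterminate row of Table 1 on the strength of the proxy alone would not be justified.

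The cost is one extra date field and a smaller sample in the sensitivity analysis. The recruitment target of 278 does not change. If all draws prove to have been made before the first pill, one sentence saying so closes the matter.
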